
Given the possibility of missing data in following participants for 12 months who may have unstable housing or community connections, imputation methods will be used to estimate the overall impact of missing data on outcomes. Administrative data from the Institute of Clinical and Evaluative will be used for the purposes of evaluating the primary outcome, and comparing the impact of missing data on outcomes.

*Economic Evaluation Plan*

The objective of the economic evaluation is to compare the cost-effectiveness of the CATCH-ED intervention with usual care, using patient-level data from the randomized clinical trial and linked administrative data at the Institute for Clinical Evaluative Sciences (ICES), Toronto. The Ontario MOHLTC perspective will be used in the analysis. In Ontario, the Ministry pays for physician visits, laboratory tests, imaging, hospitalization, emergency department visits, same day surgery/ procedure, complex continuing care and some home care services. In addition, the Ministry pays for prescription drugs for those older than 65 years old, live in a Long-Term Care Home or a Home for Special Care or enrolled in special programs such as the Ontario Disability Support Plan (ODSP). The time horizon for the economic evaluation will be 12 months (maximum follow-up of the trial).

The primary outcome will be the incremental cost per quality-adjusted life-year (QALY) gained though the intervention compared with usual care. The secondary outcomes include the incremental cost per ED visit avoided and incremental cost per hospital-day avoided.

Measuring QALYs: A QALY is a year of life experienced with a particular health-related quality of life (HRQoL) or health state utility, as represented on a scale from 0 to 1, where 0=death and 1=full health. The EQ-5D and SF-6D (converted from SF-12), generic preference-based instruments that have been used in mental health patients, will be used to assess patients’ health state utility at baseline, 6 months and 1 year. We will calculate each patient’s QALY from the utility scores using the area-under-the-curve approach, with linear interpolation between assessment points (Figure 1).

[figure not shown]

QALY0-90 days

QALY6 -12 months

QALY0-6 months

Figure 1. Calculating QALYs from EQ-5D utility scores

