Measuring resource use and costs: We will obtain the health care costs of each patient from linked administrative data at ICES (Table 1). Informed consent will be collected from each participant for linking study data to the administrative data at ICES. The two dataset will be linked using patients’ OHIP numbers.

Table 1. Data source

| **Resources** | **Sources** | **Variables** |
| --- | --- | --- |
| Hospitalization | Discharge Abstract Database | Cost estimated using Resource Intensity Weight (RIW) and cost per weighted case |
| Outpatient laboratory / imaging services and physician services (including inpatient, office and undefined service) | Ontario Health Insurance Plan (OHIP) Claims Database | OHIP billing cost estimated using utilization frequency of each service and cost per visit from OHIP fee schedule |
| Emergency Room visits / Same Day Surgery or procedure | National Ambulatory Care Reporting System (NACRS) and Same Day Surgery | Cost estimated using RIW and cost per weighted case |
| Outpatient prescription drugs | Ontario Drug Benefit Plan (ODB) | Drug cost and dispensing fee |
| Home care services | Home Care Database | Utilization frequency for each type of home care service |
| Complex continuing care | Continuing Care Reporting System | Case-mix index and duration between events or RWPD |

RWPD: RUG Weighted Patient Day is calculated by multiplying the case-mix index (CMI) and number of days for a particular RUG event. It accounts for admissions, assessments, re-entries, discharges, etc.

Calculating incremental cost per QALY gained: We will estimate average and incremental costs and QALYs for each group using multiple regressions:

[figure not shown]

[figure not shown]

where x is a vector of patient characteristics (e.g., age, sex), U­0 is the utility at baseline,10 TX­ is a treatment variable (TX=1 for intervention group), and the regression estimates β1 is the incremental cost and α1 is the incremental QALY.

Calculating incremental cost per ED visit avoided: We will estimate average and incremental costs (excluding ED visit costs) for each group using multiple regressions. The incremental cost per ED visit avoided is the incremental cost divided by the incremental number of ED presentations (more details in the statistical analysis section).

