Calculating incremental cost per hospital-day avoided: We will estimate average and incremental costs (excluding hospitalization costs) for each group using multiple regressions. The incremental cost per hospital-day avoided is the incremental cost divided by the average number of hospital-days (more details in the statistical analysis section).

Calculating net benefit regression: A treatment is cost-effective if the ICER is less than what the decision maker is willing to pay (λ) for the extra benefit (QALY gained, ED visit avoided or hospital-day avoided):

∆C/∆E <λ

We can also express this decision in terms of incremental net benefit, ∆NB:

∆NB = λ ∆E - ∆C

A treatment is cost-effective if it has a positive ∆NB, the value of the intervention’s extra benefits outweighs its extra costs. It is easier to estimate confidence interval for ∆NB because it is not a ratio. We will estimate the incremental net benefit of the intervention (β1) using multiple regressions:

NB= β0 + β1TX + β**X**

We could identify subgroups for whom the intervention is especially cost-effective using interaction terms. We will conduct net benefit regression analysis using different values of λ and will represent uncertainty using cost-effectiveness acceptability curves.

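### The two secondary cost-effectiveness ratios leave out ED or hospitalization costs that the stated Ministry perspective includes, and λ is not defined to make up for it

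*Protocol*

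**What the plan says.** All of this stands in the Protocol, Analysis Plan, Economic Evaluation Plan.

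- Perspective: "The Ontario MOHLTC perspective will be used in the analysis". The next sentence says that "the Ministry pays for physician visits, laboratory tests, imaging, hospitalization, emergency department visits" and further services.
- Outcomes: cost per QALY is primary. "The secondary outcomes include the incremental cost per ED visit avoided and incremental cost per hospital-day avoided".
- Data: Table 1 collects hospitalization costs, and takes ED costs from "National Ambulatory Care Reporting System (NACRS) and Same Day Surgery", each valued by Resource Intensity Weight (RIW) and cost per weighted case.
- ED ratio, numerator: "We will estimate average and incremental costs (excluding ED visit costs) for each group using multiple regressions". Denominator: "The incremental cost per ED visit avoided is the incremental cost divided by the incremental number of ED presentations".
- Hospital-day ratio, numerator: "We will estimate average and incremental costs (excluding hospitalization costs) for each group using multiple regressions". Denominator: "The incremental cost per hospital-day avoided is the incremental cost divided by the average number of hospital-days".
- Decision rule: the net-benefit paragraph applies one rule, ∆C/∆E < λ or equivalently ∆NB = λ∆E − ∆C > 0, to QALYs, ED visits and hospital-days. It describes λ as the decision maker's willingness to pay for the added benefit.

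No exclusion is stated for the cost-per-QALY analysis, and no reason is given for the other two.

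**The concern.** Each secondary ratio drops from its numerator the saving that its own denominator produces. What remains is the cost of everything else per visit or day avoided, which is not what the Ministry would pay, net, per visit or day avoided. The same patients would yield three different values of ∆C, all judged by one rule.

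The Ministry is to take part in discussing expansion of the programme (Protocol, Implementation). For that reader, a cost per ED visit avoided that omits the ED savings can show a price where there is a net saving, and it can disagree with the cost reported beside the QALY result.

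**Working it through.** The economic plan states no numerical result, so there is no figure to reproduce. The check is algebra with illustrative inputs.

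**Inputs.** From the protocol: the perspective, the exclusions, the denominators, and a 20% reduction in ED visit rate (Sample Size Calculation). Not in the protocol, so assumed: unit costs, mean visits and days, the change in other costs, and a 20% reduction in hospital-days.

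**Notation.** A = visits or days avoided per patient (A > 0); c = mean cost per visit or day; dO = incremental cost of everything else. Taken literally, the incremental number of presentations is negative when visits fall; the figures below use visits avoided.

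**1. ED ratio.**
- As written: dO/A.
- Full Ministry cost: (dO − cA)/A = dO/A − c.
- Difference: c, whatever dO and A are.

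Assume 10 visits per control patient, so A = 0.20 × 10 = 2.

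| dO | As written | Full, c = $150 | Full, c = $300 | Full, c = $600 |
|---|---|---|---|---|
| $500 | $250 | $100 | −$50 | −$350 |
| $1,000 | $500 | $350 | $200 | −$100 |
| $3,000 | $1,500 | $1,350 | $1,200 | $900 |

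For example, at dO = $500 and c = $300: 500/2 = 250, and (500 − 300 × 2)/2 = −50.

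**2. When the sign is wrong.** The written ratio is positive and the full ratio negative exactly when 0 < dO < cA. Here cA is $300, $600 and $1,200 for the three unit costs, so the sign reverses in three of the nine cells.

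**3. Hospital-day ratio.** With denominator D, the written ratio is dO/D and the full-cost ratio is (dO − cA)/D, so the shift is cA/D.
- If D = days avoided (A), the shift is c.
- If D = average days, as written, the shift depends on the proportional reduction r and on which average is meant: r for the control mean, r/(1 − r/2) for the mean of the two arms, r/(1 − r) for the intervention mean.

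| r | Control mean | Mean of both arms | Intervention mean |
|---|---|---|---|
| 10% | 0.100c | 0.105c | 0.111c |
| 20% | 0.200c | 0.222c | 0.250c |
| 30% | 0.300c | 0.353c | 0.429c |

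Example with 10 control days, r = 20% (A = 2), c = $1,000 and dO = $1,000. Dividing by the control mean gives 1,000/10 = $100 as written and (1,000 − 2,000)/10 = −$100 in full, a shift of $200. Dividing by days avoided gives 1,000/2 = $500 and −1,000/2 = −$500, a shift of $1,000. The condition for a wrong sign is again 0 < dO < cA, because D > 0 does not affect it.

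**4. Role of λ.** Write λ′ for willingness to pay beyond the money saved. With full costs, ∆NB = λ′A − (dO − cA) = (λ′ + c)A − dO. The excluded-cost version gives the same decision only if its λ equals λ′ + c. At λ = 0, ∆NB = −∆C, so each acceptability curve should start at the probability that the programme saves money. With three values of ∆C the curves start at different points, and the two secondary ones do not answer that question for the Ministry.

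**The case against.** The strongest defence is that the exclusion is deliberate: each ratio leaves out the cost of its own effect unit to avoid counting it twice. A payer's willingness to pay to avoid a visit may well include the visit's cost, and step 4 shows that the decision is then unchanged and only the λ axis moves by c. This is a coherent analysis, but the protocol does not set it up. It gives λ one meaning for all three effects and sets it against the programme's extra costs. The equivalence also needs a constant cost per event, whereas Table 1 values events by RIW, so differences in intensity are not recovered by a count times λ.

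Other points stand and limit the claim:

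- **Full unit cost in both ratios.** A reader might infer that each ratio is too high by the whole cost of the visit or day. The written hospital-day denominator does not support this.
- **Exactness of c.** The ED shift is only about c. Physician services are costed separately from OHIP, and it is unclear whether ED physician fees count as ED visit costs. Hospitalization is costed per weighted case, not per day, and Table 1 draws it from the Discharge Abstract Database only, while the linkage section also names the Ontario Mental Health Reporting System. Restoring hospitalization costs may not restore a full c for every day counted.
- **Net bias against CATCH-ED.** A reader might infer this too. Table 1 has no line for the cost of delivering the programme; if that cost is left out, the error runs the other way. Only the direction of the exclusion itself is established.
- **Savings hidden as a rule.** The sign reversal is conditional, and the ED ratio still contains any hospital savings.

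**Conclusion.** The point holds in limited form. The protocol fixes a Ministry perspective and then defines two secondary numerators that leave out costs inside it, without defining λ to match.

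- ED ratio: above the Ministry's net ratio by about the mean cost of an ED visit whenever visits fall, provided ED costs scale roughly with visits.
- Hospital-day ratio: also too high when days fall. The shift is a full day's cost only with days avoided as denominator; with average days it is about 0.20 to 0.25 of a day's cost at an assumed 20% reduction.
- Sign: a cost-saving programme shows a positive ratio only if other costs rise by less than the excluded savings.

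Every dollar amount and every mean count above is an assumption; the shifts are algebra. A reader might infer that the main economic conclusion is at risk. It is not: cost per QALY states no exclusion, and the trial's primary clinical outcome is untouched.

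**What to change.** 1. Use one ∆C, the full Ministry-perspective incremental cost from the cost-per-QALY regression, in all three ratios and all three net-benefit regressions.
2. Divide the hospital-day ratio by the between-group difference in hospital-days, expressed as days avoided, and express the ED denominator as visits avoided.
3. Keep the versions without ED or hospitalization costs only as labelled sensitivity analyses, with λ there defined as including the cost of the event.
4. State which items count as ED visit costs, in particular OHIP-billed ED physician fees.

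This is a change of wording. The full-cost regression is already planned and no new data are needed. The small downside is that λ for the two secondary outcomes must then be read as the value of a visit or day avoided beyond the money saved.

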Emerging evidence suggests that brief case management interventions are effective in reducing the gap between institutional and community-based care and improving continuity of care (Susser et al, 1997; Dixon et al, 2009). When continuity of care and treatment gaps are addressed, individuals with serious mental illness and/or chronic physical conditions experience improved health outcomes that are also associated with reduced hospital and community costs (Adair et al, 2005; Mitton et al, 2005; Cabana & Jee, 2004; Saultz & Lochner, 2005; Gill & Mainous, 1998; Gill et al, 2000). Similarly, both experimental and non-experimental studies support the effectiveness of case management interventions in decreasing ED visits and hospitalizations for frequent users of EDs (Shumway et al, 2009, Althaus et al, 2011). In a large before and after program evaluation of case management interventions for frequent users of EDs in 6 counties in California, a decrease of 30% in ED visits and 17% in hospital costs was achieved one year after program enrolment. Findings in year 2 of the program demonstrated further improvements, with an estimated decrease in ED visits of 60%, inpatient days of 62% and hospital costs of 62% (Linkins et al, 2008). Experimental studies have provided further support for the effectiveness of case management interventions (Althaus, 2011). A randomized controlled trial of 252 frequent users by Shumway confirmed significant reductions in ED use and ED costs 12 months after enrolment in a case management program. The intervention also led to significant decreases in homelessness and alcohol use and improvements in accessing income support and health cards (Shumway, 2008). A recent systematic review by Althaus concluded that it may be beneficial to patients and economically justifiable for hospitals to implement case management for frequent users (Althaus, 2011).

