*Colorado Symptom Index (CSI):* The CSI was designed specifically for individuals with mental health problems. It is a 14-item instrument which assesses the presence and frequency of symptoms of mental illness experienced within the past month. Responses are provided using a 5-point Likert scale with answer choices ranging from 0 (not at all) to 4 (at least every day). A higher score indicates a higher level of symptoms. The Colorado Symptom Index is a widely used tool in research as a self-report measure of psychiatric symptomatology. The CSI has been reported to have excellent internal consistency (.92) and test-retest reliability (.71). Evidence of the CSI’s validity is strong as CSI scores have been proven to distinguish between individuals with and without mental health service needs and were significantly correlated with functioning(Boothroyd and Chen, 2008).

*ASI:* The alcohol and drug module of the Addiction Severity Index (ASI), the most widely used instrument in the field, will be utilized. The ASI is a structured interview instrument that yields information about the severity of lifetime and recent (previous 30 days) drug and alcohol use (McLellan et al, 1980). Five indices will be used to measure substance abuse-the number of days that alcohol or substances were abused in the past month, the amount of money spent on alcohol or drugs in the past month, and the participants’ rating of the need for alcohol or drug use treatment. The ASI has good inter-rater and test-retest reliability and good concurrent and discriminant validity. It has been used extensively with the homeless population (Hwang et al, 2005).

*Participant Service Use:* Service use events will be tracked using both self-reported and administrative data. We will establish the number of hospitalizations, days in hospital and emergency department visits during the year prior to program enrolment as well as the 12 month follow-up period. We will also collect data on non-acute service use, such as mental health, substance use, and primary care visits, using service use forms adapted from the At Home / Chez Soi project on homelessness and mental health.

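### The cost per hospital-day avoided is defined with average hospital-days as its denominator, which contradicts the protocol's own ICER rule and its parallel ED-visit definition

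*Protocol*

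**What the plan says.** Under Economic Evaluation Plan, the protocol names cost per QALY as the primary economic outcome and adds: "The secondary outcomes include the incremental cost per ED visit avoided and incremental cost per hospital-day avoided".

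The three ratios are then defined one by one.

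- **QALY:** costs and QALYs are each regressed on a treatment indicator. The two treatment coefficients are the incremental cost and the incremental QALY.
- **ED visits:** "The incremental cost per ED visit avoided is the incremental cost divided by the incremental number of ED presentations".
- **Hospital-days:** for the numerator, "We will estimate average and incremental costs (excluding hospitalization costs) for each group using multiple regressions". For the ratio, "The incremental cost per hospital-day avoided is the incremental cost divided by the average number of hospital-days".

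The net benefit paragraph then gives the general rule: a treatment is cost-effective if ∆C/∆E is below the willingness to pay λ. It lists the effects to which this applies: "QALY gained, ED visit avoided or hospital-day avoided". The same rule is restated as ∆NB = λ∆E − ∆C.

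**The concern.** A cost per unit avoided needs the number of units avoided in its denominator, here the between-arm difference in hospital-days. Dividing by an average gives incremental cost per day *used*, reported as cost per day *avoided*. Of the three ratios, only this one lacks an incremental denominator.

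Two things are at stake. First, the reported figure would have the wrong size, and the reader could not tell by how much. Second, the formula does not respond properly to the effect it is meant to price. Average days are positive whether the programme shortens hospital stay, leaves it unchanged or lengthens it. The ratio would therefore be finite and look normal in all three cases, and could be compared with λ as if days had been avoided.

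**Working it through.** The protocol states no numerical ICER, so there is no figure to reproduce. The check is algebra, followed by an illustration with assumed inputs.

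**Inputs.** The two ratio definitions and the ∆C/∆E rule come from the Economic Evaluation Plan. The protocol gives no incremental cost, mean hospital-days or expected reduction in days for this trial. Assumed: a usual-care mean of 10 days, ∆C of +1,000 or −1,000 dollars, and a range of relative reductions r. The 62% row uses the year-2 fall in inpatient days that the Background reports from a before-after evaluation; it only marks a large reduction and is not a forecast.

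**Algebra.** Let U be mean days in usual care, T = U(1 − r) mean days in the intervention arm, and D the average used as denominator.

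- Correct ratio: ∆C / (U − T) = ∆C / (rU)
- Stated ratio: ∆C / D
- Stated ÷ correct = rU / D, that is, days avoided ÷ mean days

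The protocol does not say which average D is. With equal arms:

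- D = U (usual-care mean): factor r
- D = U(1 − r/2) (pooled mean): factor r / (1 − r/2)
- D = U(1 − r) (intervention mean): factor r / (1 − r)

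| Reduction r | Usual-care mean | Pooled mean | Intervention mean |
| --- | --- | --- | --- |
| 10% | 0.10 | 0.11 | 0.11 |
| 20% | 0.20 | 0.22 | 0.25 |
| 30% | 0.30 | 0.35 | 0.43 |
| 50% | 0.50 | 0.67 | 1.00 |
| 62% | 0.62 | 0.90 | 1.63 |
| 70% | 0.70 | 1.08 | 2.33 |

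The factor reaches 1 at r = 2/3 with the pooled mean and at r = 1/2 with the intervention mean. With the usual-care mean it stays below 1 for any reduction short of 100%.

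**Illustration in dollars** (usual-care mean 10 days; stated values in the order usual-care / pooled / intervention mean):

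| ∆C | Days, usual care vs CATCH-ED | Correct ratio | Stated ratio |
| --- | --- | --- | --- |
| +1,000 | 10 vs 8 | 1,000/2 = 500 | 100 / 111 / 125 |
| +1,000 | 10 vs 10 | undefined (1,000/0) | 100 / 100 / 100 |
| +1,000 | 10 vs 11 | 1,000/(−1) = −1,000, dominated | 100 / 95 / 91 |
| −1,000 | 10 vs 8 | −1,000/2 = −500 | −100 / −111 / −125 |
| −1,000 | 10 vs 11 | −1,000/(−1) = 1,000 saved per extra day | −100 / −95 / −91 |

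In the first row the stated ratio is 4 to 5 times too low. In the second and third rows no days are avoided, yet the result differs little from the first. In the fourth row the error runs the other way: the saving per day avoided is understated. In the last row a programme that saves money but uses more days shows the same sign as one that saves money and avoids days.

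**Does the cross-reference cure it?** The hospital-day sentence points to the statistical analysis section for detail. The Analysis Plan says only that days in hospital is a count outcome, to be analysed by Poisson or negative binomial regression for a treatment effect. It does not redefine the denominator.

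**The case against.** The strongest reply is that this is a one-word slip. The general rule two paragraphs later names the hospital-day avoided as an effect, the ED sentence uses the incremental number, and any health economist would see what was meant. The net benefit regression, which carries the formal inference and the acceptability curves, takes the treatment coefficient as its estimate and so does not inherit the error. The primary economic outcome is cost per QALY, and its denominator is incremental. All of this stands, and it limits the importance of the point. It does not make the sentence right: this is the only definition given of a declared outcome, and an analyst who followed it would report a wrong number.

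A reader might infer two stronger things, and the protocol supports neither.

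- **That the formula nearly always flatters the intervention.** This needs a positive ∆C, and the protocol does not fix the sign. The numerator leaves out hospitalization costs, Table 1 has no line for the cost of the programme itself, and fewer ED visits are hypothesized, so a negative ∆C is possible. Even with a positive ∆C, the direction reverses for reductions above about 67% (pooled mean) or 50% (intervention mean).
- **That the ED ratio has the wrong sign,** because intervention minus control is negative when visits fall. The protocol states no order of subtraction for that denominator, the ratio is named as a cost per visit avoided, and the decision rule defines the effect as a visit avoided. The ED wording is loose but not wrong.

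**Conclusion.** The definition is wrong as written and contradicts the protocol's own rule. It should be corrected before analysis, but it does not threaten the trial's main economic or clinical conclusions.

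The size is days avoided divided by mean days: about 0.10 to 0.43 of the correct ratio for assumed reductions of 10% to 30%, over the three possible averages. This factor does not depend on the assumed dollar amount or on the assumed 10 days; it depends only on the relative reduction and on which average is used.

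With a positive incremental cost and fewer days, the error usually makes the programme look cheaper per day avoided than it is. With a negative incremental cost and fewer days, it usually understates the saving. The firmest part of the finding needs no assumed figures: whenever incremental cost is not zero, the formula cannot show that no days were avoided or that days rose.

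**What to change.** In the paragraph on cost per hospital-day avoided, replace the denominator with *incremental number of hospital-days avoided (usual care minus CATCH-ED)*. For consistency, word the denominator of the ED ratio as *ED visits avoided (usual care minus CATCH-ED)*, so that both ratios match the effects listed under the ∆C/∆E rule. The net benefit formula needs no change.

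The cost is two phrases. No new data are needed: the protocol already plans to collect the counts ("We will establish the number of hospitalizations, days in hospital and emergency department visits during the year prior to program enrolment") and the same for the 12-month follow-up. The difference in mean days can be derived from the treatment-effect model already planned for days in hospital. Sample size and schedule are unaffected.
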